## Aims

The BE WELL (*B*reathe *E*asier through *We*ight *L*oss *L*ifestyle) intervention trial was designed to address the gap in knowledge of whether weight loss improves asthma control. It aims to evaluate the efficacy of an evidence-based, comprehensive weight loss lifestyle intervention as adjunct therapy to usual care in the management of asthma in obese adults. The primary hypothesis is that compared with participants in the usual care (UC) arm, those in the weight loss intervention (WL) arm will achieve greater improvement in asthma control, as measured by a validated composite measure, the Juniper Asthma Control Questionnaire (ACQ) [28], at 12 months follow-up. Secondary aims include comparing the WL and UC arms on changes in ACQ scores at six months and in lung function, asthma-specific quality of life (QoL), asthma medication use, and asthma-related health care utilization (HCU) at six and 12 months. Potential mediators (e.g. weight loss and change in physical activity level and diet composition) and moderators (e.g., socio-demographic characteristics and comorbidities) of the intervention effects will be explored.

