**Data from KPNC Electronic Databases**			
Current medical problems	X		X
Medications currently prescribed	X	X	X
Medications dispensed^2^	X		X
Health care utilization^2^	X		X
Primary care provider characteristics	X		X

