**Recruitment and intervention process measures (monitored continuously)**			
**Safety of participants in the intervention arm (monitored continuously)**			

^1^Pre- and post-bronchodilator spirometry will be obtained at baseline visit 1 to determine reversibility of airway obstruction, which is an eligibility criterion. Only pre-bronchodilator spirometry will be performed at baseline visit 2 and at 6- and 12-month assessments and the measurements obtained will be used for analysis.

^2^Data will be extracted for a period of 12 months before and after randomization.

Abbreviations: ERV, expiratory reserve volume; FEV1, forced expiratory volume in one second; FEV6, forced expiratory volume in six seconds; FVC, forced vital capacity; IC, inspiratory capacity; KPNC, Kaiser Permanente in Northern California; VCin and VCex, inspiratory and expiratory vital capacity; VT, tidal volume.

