Secondary outcomes include lung function measurements by spirometry (Table 2) and the 15-item Juniper Mini Asthma Quality of Life Questionnaire (mini-AQLQ) [32]. In addition, asthma-related health care utilization (HCU) will be assessed through data extraction from KPNC electronic databases for the period of 12 months pre- and post-randomization. These databases contain information on all outpatient and inpatient HCU at KP facilities, non-KP facilities with which KP contracts for emergency and hospital services, and on reimbursable emergency hospital care at non-contract facilities. Although we will analyze HCU data according to type of encounter, the primary HCU outcome will be the overall rate of outpatient encounters and emergency department and inpatient admissions with asthma as primary diagnosis. Data will also be extracted on current medications prescribed and all asthma, allergic rhinitis, and GERD medications dispensed for the same time periods. In KP, it is estimated that well over 95% of all prescriptions are filled at a KP pharmacy, and patients are very unlikely to have concurrent non-KP sources of asthma care or pharmacy. Therefore, dispensing records provide reliable and unbiased information on medication refill adherence and regimen potency. The former will be assessed by calculating continuous medication acquisition indices (the total days supply of a given type of medication dispensed in a given period of time as a proportion of the total days supply prescribed), for asthma controller and reliever medications separately. The total strength of all controller medications dispensed in a given time period will be expressed in beclomethasone-80 canister equivalents, and the total strength of all reliever medications dispensed in a given time period will be expressed in albuterol canister equivalents, as we have done in our previous research [33]. For combination medications (e.g., fluticasone-salmeterol), each active ingredient component of the medication will be counted separately and all will contribute to the adherence and potency calculations.

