#### Statistical analysis

The primary hypothesis compares Juniper ACQ scores between the WL and UC arms at 12 months using an intent-to-treat analysis. Linear mixed modeling, using SAS PROC MIXED [67] will test time and group interactions to assess whether within-subject change in Juniper ACQ scores differs by condition (equation 3).(3)

Due to randomization, the distributions of baseline values on the dependent variable (Y_0_) and baseline covariates (X_i _where i = 1 to k) should be similar between treatment arms and thus not bias the analysis. Nonetheless, to the extent they are associated with the outcome, their inclusion in the model will account for otherwise unexplained variation and hence increase the efficiency of the analysis. In addition, their inclusion will guard against imbalance in the distributions of these covariates between treatment arms, which can still occur despite randomization. a, g, and δ represent the random effects caused by clustering of patients with physicians and, in turn, physicians within clinics, and by blocking of patients within medical centers. ε takes into account the correlation of repeated measures within subjects.

The same analysis strategy is appropriate for evaluating secondary aims where the hypotheses are identical but with different outcome measures (e.g., lung function, asthma-specific QoL, asthma-related HCU). The longitudinal effects of the intervention will be assessed using the same model, except that the focus is comparisons within the intervention arm at different time points. Analyses will also be conducted to examine whether there is a dose-response relationship between intervention adherence and outcome, where dose is defined in terms of number of group sessions attended, number of self-monitoring logs kept, average daily intakes of calories and fat, and average number of minutes of physical activity per week.

The primary analyses will be intention-to-treat. Secondary per-protocol or as-treated analyses will be performed to help elucidate the primary findings. For subjects with missing data at follow-up, we will conduct and report on sensitivity analyses in which several previously recommended approaches for handling missing data in longitudinal trials will be used, e.g., multiple imputation and the pattern-mixture model [68].

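### Asthma-related health care utilization is promised at six and 12 months but scheduled as one 12-month post period, and this encounter rate is assigned the linear repeated-measures model written for ACQ

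*Protocol article*

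**What the plan says.** **Aims.** The secondary aims include comparing the weight loss (WL) and usual care (UC) arms on change in "asthma medication use, and asthma-related health care utilization (HCU) at six and 12 months".

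**Primary and Secondary Outcomes.** HCU is extracted from electronic databases "for the period of 12 months pre- and post-randomization", and "the primary HCU outcome will be the overall rate of outpatient encounters and emergency department and inpatient admissions with asthma as primary diagnosis".

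**Table 2.** The HCU row is marked at baseline and month 12, and its month-6 cell is empty. Footnote 2, attached to that row, reads "Data will be extracted for a period of 12 months before and after randomization".

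**Statistical analysis.** For ACQ, "Linear mixed modeling, using SAS PROC MIXED [67] will test time and group interactions". The surrounding text includes the baseline value of the outcome (Y_0) as a covariate and has the residual term carry the correlation of repeated measures. It then says "The same analysis strategy is appropriate for evaluating secondary aims where the hypotheses are identical but with different outcome measures", with lung function, asthma-specific quality of life and asthma-related HCU as examples. No count distribution, log link, transformation or person-time offset is mentioned.

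**The concern.** There are two separate problems.

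1. **Aim against schedule.** The Aims need an HCU value at month 6. The schedule and the outcome definition provide one undivided post-randomization year. The empty month-6 cell does not look like a slip, because in the same block of Table 2 the currently prescribed medications are marked at month 6.

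2. **Model against outcome.** A linear model with repeated-measures residuals and time-by-group terms suits a score measured at each visit. HCU is a count of encounters over a period. It is likely to contain many zeros and a long right tail, and its variance is likely to rise with its mean. Observed time can also differ between participants, for example if someone leaves the health plan. A linear model on annualized rates gives a short observation period the same weight as a full year. On unadjusted counts it treats unobserved time as time without encounters.

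At stake are a promised six-month result that has no defined data, and an HCU effect estimate on an additive scale that a few heavy users can drive.

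**Working it through.** **1. The plan's own figures.** The article gives no event rate, power or sample size for HCU. Its only calculation is for an effect size of 0.4 at two-sided 5% alpha: 324 randomized, 324 x 0.8 = 259 completers, 90% power. A t-test with 259 participants has power 0.894, so that figure reproduces. It has no bearing on HCU except to fix the number of participants.

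**2. Counting HCU values per participant.**

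| Source | Pre | Month 6 | Month 12 |
|---|---|---|---|
| Aims | change implied | yes | yes |
| Table 2, HCU row | yes | empty | yes |
| Table 2 footnote 2; outcome text | one 12-month window | not defined | one 12-month window |

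The schedule yields 2 values: one pre and one post. If the pre value is Y_0, then 2 - 1 = 1 response remains. With one response per participant there is no within-subject residual correlation to estimate and no time-by-group term. What is left is an ANCOVA of the 12-month count or rate on arm and baseline. Equation 3 is not visible in the text at hand, so its terms are taken from the description around it.

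**3. How badly a linear model describes such counts.** All inputs here are assumptions. Pre and post counts were simulated as Poisson with a shared gamma frailty (mean 1, variance k). The post period had extra gamma variation (mean 1, variance 0.5). Settings were N = 324, equal arms, full follow-up and 1,000 runs each. The linear model was ANCOVA on the pre count. The count model was a log-link Poisson with robust standard errors (SE) and log(pre + 0.5) as covariate.

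| Rate/year | k | Zeros, null / rate ratio 0.7 | Null rejection, linear / count | Power at rate ratio 0.7, linear / count |
|---|---|---|---|---|
| 0.5 | 1 | 70% / 73% | 0.053 / 0.059 | 0.368 / 0.382 |
| 0.5 | 2 | 74% / 76% | 0.054 / 0.070 | 0.290 / 0.318 |
| 1 | 1 | 55% / 59% | 0.049 / 0.059 | 0.490 / 0.515 |
| 1 | 2 | 62% / 65% | 0.033 / 0.051 | 0.409 / 0.447 |
| 2 | 1 | 40% / 44% | 0.041 / 0.049 | 0.627 / 0.657 |
| 2 | 2 | 50% / 53% | 0.050 / 0.068 | 0.532 / 0.563 |

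Between 40% and 76% of participants have no encounters, and the skewness of the linear residuals is 2.5 to 3.3. Normal errors are therefore a poor description. The linear test nevertheless keeps its size (0.033 to 0.054). The count model's power advantage runs from 0.382 - 0.368 = 1.4 points to 0.447 - 0.409 = 3.8 points.

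**4. Whether the power difference is stable.** Other assumptions, again with a rate ratio of 0.7 and with 15% partial follow-up, give other answers:

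- Rates 1.5 to 3, overdispersion 1 to 1.5, 300 runs, negative binomial without robust SE. Linear / count power was 0.56/0.61, 0.45/0.55 and 0.70/0.78, a gain of 5 to 10 points. Null rejection was 7-8% for the count model against 3-7% for the linear one, so part of that gain reflects a test that rejects too often.
- The same rates and dispersion with one frailty fully shared between periods, robust SE, 1,000 runs. Power was 0.77/0.78, 0.78/0.77 and 0.97/0.96, which is no gain.
- Rates 0.5 to 3 with frailty sharing between periods varied from 0.3 to 1. Robust negative binomial power ran from about 3 points above the linear model to 12 points below it, while the linear test's size was 0.034 to 0.064.

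The sign of the difference depends on inputs that the article does not give, among them how far a person's encounter rate persists from one year to the next.

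**The case against.** **The six-month data exist.** Encounters come from electronic records covering all 12 months after randomization. If encounter dates are kept, the year can be split at six months with no new collection, and the empty cell in Table 2 may only mark when extraction takes place. This stands in part. A reader might infer that the six-month comparison cannot be produced, and the article does not support that. What it lacks is a definition of the six-month value.

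**A time-by-group term can be fitted.** It can, with two post windows, or with pre and post both treated as responses. This also stands. The term disappears only under the reading with Y_0 as covariate and one post value. That is, however, the reading that the text and schedule together describe.

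**A shared strategy need not mean PROC MIXED on raw counts.** It could mean intention-to-treat, baseline adjustment and clustering terms, with the distribution left to a fuller document. This is weak. The sentence directly follows the PROC MIXED description, names HCU, and is followed by a reference to the same model. The article makes a positive statement about HCU here and does not merely stay silent.

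**Unequal person-time may be rare.** Members need at least one year of membership, those planning to transfer care are excluded, and a missed study visit does not shorten the records. This stands as to size. The exclusion covers only planned departures, though, and no rule is given for those who do leave.

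**A difference in mean encounters is a valid randomized comparison at about 162 per arm.** This stands. The case for a count model rests on fit, exposure and interpretation.

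**Conclusion.** The point holds in two limited parts. The Aims and the schedule disagree on whether HCU has a six-month value; this follows from the text and needs no assumption. The article also endorses for an encounter rate a linear repeated-measures model which, with the pre-period value as Y_0, has a single response per participant and no stated treatment of unequal observation time. This second part assumes that Equation 3 matches the text around it.

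Two stronger readings should be avoided. A reader might infer that the linear test gives too many false positives, but across the assumptions tried its null rejection was about 3% to 7%. A reader might also infer that a count model would add power. The simulated differences run from a 10-point gain to a 12-point loss, and without event rates in the article no reliable gain can be claimed.

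The consequence is confined to a secondary outcome. The six-month HCU result is undefined, and the HCU effect is described on a scale and with an error model that suit it poorly. This should be corrected, but it does not threaten the trial's main conclusion.

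**What to change.** 1. **Reconcile aim and schedule.** Either define HCU windows for months 1-6 and 7-12 from the dated encounters and add a month-6 HCU entry to Table 2, or limit the HCU aim to 12 months. Apply the same decision to dispensed medications, whose row has the same empty month-6 cell and the same footnote.

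2. **State a count model for HCU.** Use a log-link model (negative binomial, or Poisson with robust SE) of post-randomization encounters on arm. Include log person-time as offset, and the pre-period count (in a form fixed in advance) and the balancing factors as covariates. Report a rate ratio with its confidence interval. With two windows, use a repeated-measures version such as GEE with a window-by-arm term. Say how the physician, clinic and medical-center terms carry over from the ACQ model.

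3. **Reword the extension sentence** so that the linear mixed model covers the continuous secondary outcomes and HCU has its own statement.

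The cost is a few sentences and different SAS code (PROC GENMOD or GLIMMIX) on data already due for extraction. The result will be on a ratio scale, so a difference in mean encounters can be added for readers who want absolute numbers. No new data are needed, and the ACQ analysis and sample size stay as they are.

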### Eligibility Criteria

Participants will be recruited from multiple medical centers of Kaiser Permanente in Northern California (KPNC). Patients ages 18-70 years who are obese and have suboptimally controlled, persistent asthma will be eligible to participate. Table 1 enumerates the inclusion and exclusion criteria. Exclusion criteria were designed to ensure each participant's ability and safety to complete the study requirements, minimize error associated with primary outcome, and prevent possible missing data. Individuals of both genders and any racial or ethnic background who speak English, meet the inclusion criteria, and have no exclusion criteria will be eligible. Based on the demographics of obese asthma patients at the selected KPNC sites, the gender and ethnic distributions of the target enrollment population are expected to consist of 67% women, 57% White, 27% Black, 7% Hispanic/Latino, and 9% Asian/Pacific Islander.

**Table 1 T1:** Participant inclusion and exclusion criteria

Inclusion criteria
* Age (as of date of enrollment)
- Lower age limit: 18 years
- Upper age limit: 70 years
* Gender: Both men and women
* Race/ethnicity: All racial and ethnic groups
* Body mass index 30.0-44.9 kg/m^2^
* Suboptimally controlled asthma:
- Documented diagnosis of asthma on the current medical problem list
- Currently prescribed an anti-asthma medication
- Score <20 on the Asthma Control Test [75]
- Demonstrable airway reversibility
* Kaiser member for ≥ 1 year
* Able and willing to enroll and provide written, informed consent, i.e., to: 1) meet the time and data collection requirements of the study; 2) be randomized to one of the two intervention arms; 3) adhere to the recommendations of the study intervention as assigned; 4) participate in follow-up for 12 months; and 5) allow extraction of relevant information from their medical records.
Exclusion criteria
* Inability to speak, read or understand English;
* Intermittent asthma, defined as either seasonal asthma or (daytime asthma symptoms <2×/week and nocturnal symptoms <2×/month and no use of controller medications);
* Diagnosis of COPD (emphysema or chronic bronchitis) suggested by patient report of doctor diagnosis, spirometry, and smoking history;
* Use of weight-loss medications in the past 3 months;
* Initiation or change of antidepressant medication within the past 3 months;

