### Recruitment and Screening Process

The target sample size for BE WELL is 324, to be recruited in five sequential cohorts. Recruitment for each cohort will begin by querying KPNC's electronic asthma registry to identify obese adult patients who are likely to have suboptimally controlled, persistent asthma based on them past ER visits, hospitalizations, and/or medication dispensing records. These patients will be reviewed by their primary care provider (PCP) to determine whether their participation in the study is medically appropriate and safe. Patients for whom PCP approval is obtained will be invited by mail to participate in the study and be asked to complete, either online or by phone, a brief eligibility screening questionnaire pertaining primarily to major exclusions that patients can reliably answer on their own (e.g., pregnancy, plans to move, active cancer). Patients who pass the initial screen will be scheduled for a formal in-person eligibility determination visit (BV1) and, if eligible, a second visit (BV2) to complete baseline data collection prior to randomization.

BV1 will occur no more than four months after the initial screen, and no more than two months prior to BV2. Written informed consent will be obtained, followed by completion of additional eligibility questionnaires, including screening for angina, peripheral vascular disease (PVD), and severe depression. Height and weight will be measured and BMI calculated. Patients whose BMI is in the eligibility range between 30.0-44.9 kg/m^2 ^will have spirometry performed before and after administration of a short-acting beta agonist to determine reversibility of airway obstruction. Patients with very poor lung function (pre-bronchodilator forced expiratory volume in one second [FEV1]<40% of predicted or post-bronchodilator FEV1<50% of predicted) or who have possible angina, PVD, or severe depression will be referred to a study physician and their PCP for evaluation and may only continue in the study with explicit physician authorization. Participants who prove fully eligible will be given instructions, a two-week asthma diary form, and a three-day food record form to be completed and returned at BV2.

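### The additional analysis of longitudinal effects relies on change within the weight-loss arm, so change shared with usual care would be reported as an intervention effect

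*Protocol article*

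**What the plan says.** The Statistical analysis section sets out three things in turn.

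- **Primary analysis.** "The primary hypothesis compares Juniper ACQ scores between the WL and UC arms at 12 months using an intent-to-treat analysis". The mixed model "will test time and group interactions to assess whether within-subject change in Juniper ACQ scores differs by condition".
- **Secondary outcomes.** The same strategy is applied to them. The Aims section confirms that these comparisons are also between arms: "Secondary aims include comparing the WL and UC arms on changes in ACQ scores at six months and in lung function", followed by quality of life, medication use and asthma-related utilization at six and 12 months.
- **Longitudinal effects.** These are to be assessed with the same model, "except that the focus is comparisons within the intervention arm at different time points". The time points are not named, and nothing in the article gives the result a purely descriptive role.

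Three other sections bear on how to read a change within WL. Table 1 (Eligibility Criteria) requires "Score <20 on the Asthma Control Test". The section on intervention format states that both arms continue standard care and receive a pedometer, a home scale, and asthma and weight handouts. The data collection section schedules the 6- and 12-month visits for both arms.

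**The concern.** A before-after change in one arm mixes the effect of the intervention with everything else that changes over the same period. Here that includes:

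- regression to the mean, because entry requires poor asthma control at screening;
- the effect of continued usual care and of the materials given to both arms;
- seasonal change, for contrasts that involve month 6.

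UC is exposed to all of these at the same visits, so the WL-minus-UC contrast removes them to the extent that they are shared. The within-WL comparison does not.

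At stake are statements about the course of the effect over time. A fall in ACQ within WL could be reported as a longitudinal intervention effect although UC fell equally. The reverse error is also possible: stable WL scores from month 6 to month 12 could be read as a maintained effect while UC was catching up. The wording matters because the Background criticises earlier weight-loss research for lack of randomization, and the Discussion presents the study of longitudinal effects as a main contribution of this trial.

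**Working it through.** **1. The plan's own figure.** The Sample Size section gives 324 participants for d = 0.4, 90% power, two-sided 5% alpha and 20% loss, leaving 259 completers.

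- n per arm = 2(1.96 + 1.2816)² / 0.4² = 131.3, rounded up to 132, so 264 completers. 264 / 0.8 = 330, which is within 3% of 324.
- 324 × 0.8 = 259.2, which matches 259, or about 129.5 per arm.
- Power at 129.5 per arm: Φ(0.4 × √(129.5/2) − 1.96) = Φ(1.26) = 89.6%; by the t-test 89.4%.

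The stated size therefore reproduces closely. It refers to the WL-versus-UC comparison only.

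**2. Illustration of the within-arm test when the intervention has no effect.**

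Input from the document: about 130 WL completers (259 / 2).

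Assumed, because the document gives no value:
- both arms improve equally from baseline by s = 0.1 or 0.2 SD;
- the baseline-to-12-month correlation is ρ = 0.5 or 0.6;
- the SD is equal at the two times;
- the comparison is a paired baseline-to-12-month test.

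The SD of individual change is √(2(1 − ρ)), so z = s√130 / √(2(1 − ρ)). The rejection probability is Φ(z − 1.96) + Φ(−z − 1.96).

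| s (SD) | ρ | z | Within-WL rejection | Between-arm rejection |
|---|---|---|---|---|
| 0.1 | 0.5 | 1.14 | 21% | 5% |
| 0.1 | 0.6 | 1.27 | 25% | 5% |
| 0.2 | 0.5 | 2.28 | 63% | 5% |
| 0.2 | 0.6 | 2.55 | 72% | 5% |

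A noncentral-t calculation with 129 completers gives 20% and 62% for the two rows with ρ = 0.5.

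**3. Could selection alone produce a drift of this order?** If selection is on a screening measure, the expected drift is the depth of selection × (correlation with baseline − correlation with month 12). Assume that the worst 30% or the worst 50% are selected, which gives a mean depth of 1.16 or 0.80 SD. Assume a correlation of 0.7 with the baseline visit (BV2) and of 0.6, 0.5 or 0.4 with month 12.

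- Worst 30%: 0.12, 0.23, 0.35 SD.
- Worst 50%: 0.08, 0.16, 0.24 SD.

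A drift of 0.1 to 0.2 SD is thus possible without extreme inputs, but every input in this step is an assumption.

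**The case against.** The strongest reply is that this is one additional analysis in a plan whose inferential comparisons are already randomized. No aim or hypothesis depends on it. It uses the same model, which contains both arms, with a different focus. That stands, and it limits the point to claims about the course over time.

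A second reply is that the intended comparison may be month 6 against month 12, that is, maintenance after the intensive stage. The section treats the baseline value of the outcome as a covariate, which fits that reading. Regression to the mean from screening would then be smaller, and the baseline-to-12-month illustration would not describe the planned test. The model equation is not legible and the time points are not named, so this cannot be settled. A 6-to-12-month change within WL would still carry seasonal and other shared change.

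Third, some regression may occur before baseline. BV2 is at least two weeks after the screening visit, and the selecting instrument (the Asthma Control Test) is not the outcome (ACQ). This lowers the expected drift but does not remove it.

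Three stronger readings are tempting, and the documents do not support them:

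- **That the plan discards its control arm, or judges effects over time only within WL.** The 6- and 12-month comparisons in the Aims are between arms.
- **That the emergency visits and admissions used to find patients necessarily lie in the 12-month pre-randomization period that serves as the utilization baseline.** The registry query looks for patients "likely to have suboptimally controlled, persistent asthma based on them past ER visits, hospitalizations, and/or medication dispensing records". It gives no look-back window and allows identification from dispensing alone, and Table 1 has no utilization criterion. Overlap is possible but not stated.
- **That season biases every contrast.** BV2 is at most four weeks before the intervention starts, and the last visit is 12 months after randomization, so those two visits fall at about the same time of year. Only contrasts with month 6 are exposed, and their direction across five sequential cohorts is unknown.

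**Conclusion.** The point holds, with limited scope. As written, the plan attributes change within WL to the intervention in its longitudinal analysis, although a randomized control is measured at the same visits. The primary 12-month ACQ test, the stated secondary aims and the sample size are unaffected.

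The 21% to 72% range only illustrates how easily a modest shared improvement becomes statistically significant within one arm. It rests on the assumed drift and correlation and on an assumed baseline-to-12-month comparison, and is not an error rate that can be derived from the protocol. The conclusion itself needs only that some change is common to both arms, which the entry criteria and the shared care make plausible. The sentence should be changed, but the trial's main inference does not depend on it.

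**What to change.** Replace the sentence on longitudinal effects so that it:

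- defines them, from the same mixed model, as the already planned WL-minus-UC contrasts at 6 and 12 months, plus the between-arm difference in change from month 6 to month 12 as the measure of maintenance;
- names these time points;
- states that change within WL will be shown descriptively, preferably beside the change within UC, and not reported as an effect of the intervention.

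Only the 6-to-12-month between-arm contrast and the descriptive label are new. The cost is a sentence or two of text, with no new data, model or participants.
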